## Abstract

**Introduction:**

Purrble, a socially assistive robot, was codesigned with children to support in situ emotion regulation. Preliminary evidence has found that LGBTQ+ youth are receptive to Purrble and find it to be an acceptable intervention to assist with emotion dysregulation and their experiences of self-harm. The present study is designed to evaluate the impact of access to Purrble among LGBTQ+ youth who have self-harmful thoughts, when compared with waitlist controls.

**Methods and analysis:**

The study is a single-blind, randomised control trial comparing access to the Purrble robot with waitlist control. A total of 168 LGBTQ+ youth aged 16–25 years with current self-harmful ideation will be recruited, all based within the UK. The primary outcome is emotion dysregulation (Difficulties with Emotion Regulation Scale-8) measured weekly across a 13-week period, including three pre-deployment timepoints. Secondary outcomes include self-harm (Self-Harm Questionnaire), anxiety (Generalised Anxiety Disorder-7) and depression (Patient Health Questionnaire-9). We will conduct analyses using linear mixed models to assess primary and secondary hypotheses. Intervention participants will have unlimited access to Purrble over the deployment period, which can be used as much or as little as they like. After all assessments, control participants will receive their Purrble, with all participants keeping the robot after the end of the study. After the study has ended, a subset of participants will be invited to participate in semistructured interviews to explore engagement and appropriation of Purrble, considering the young people’s own views of Purrble as an intervention device.

**Ethics and dissemination:**

Ethical approval was received from King’s College London (RESCM-22/23-34570). Findings will be disseminated in peer review open access journals and at academic conferences.

**Trial registration number:**

NCT06025942.

STRENGTHS AND LIMITATIONS OF THIS STUDYThis is the first randomised controlled trial to explore the impact of access of Purrble, a socially assistive robot, compared with waitlist control on emotion regulation (ER) difficulties within LGBTQ+ youth who have current experiences of self-harmful ideation.Purrble was codesigned with youth to support ER in situ.The study was codesigned with young people who have experience of mental health difficulties (Sprouting Minds), including a detailed safeguarding procedure.Participants will not be blinded to participant group due to the nature of the intervention.

## Introduction

Self-harm, defined as the intentional poisoning or injury of self, irrespective of intention,^1^ is a key health concern among sexual orientation and/or gender identity minorities, LGBTQ+ populations.^2^ Internationally, young LGBTQ+ people report higher prevalence of self-harmful thoughts and behaviours, anxiety, depression and substance misuse when compared with their cisgender, heterosexual peers.^3–8^ It is well documented that those with a history of self-harm are at greater risk of suicide,^9^ and recent evidence indicates that LGBTQ+ youth are 3–6 times more likely attempt suicide than their cisgender, heterosexual counterparts.^10 11^ Despite the considerable risk of self-harm and associated adverse outcomes,^12 13^ there is a lack of evidence-based interventions to support LGBTQ+ youth struggling with self-harmful thoughts and behaviours.

Youth who self-harm often do not seek professional help^14 15^ and those that do find services (eg, Child and Adolescent Mental Health Services, Accident and Emergency or social services) to be less helpful sources of support^16^ or rarely reattend services.^17^ Factors relating to this can include negative attitudes and behaviours/treatment from healthcare staff (eg, withdrawing pain-reducing medication for wound treatment^18^), concerns about confidentiality^19^ or perceived stigma surrounding self-harm.^20 21^ Among LGBTQ+ people, help-seeking is even more complex, with one in seven avoiding services due to fears of discrimination on the basis of their sexual orientation or gender identity.^22^ Therefore, community-based interventions may be more appropriate to support LGBTQ+ youth engaging in self-harm.

As LGBTQ+ youth are frequent users of digital technologies,^23–26^ there is an opportunity for digital interventions to support those struggling with self-harm and other mental health difficulties. Evidence suggests that digital interventions support youth to bypass various barriers to help-seeking, such as lack of accessibility, anticipated stigma, inadequate resources and the desire to be self-reliant,^27^ which are compounded by unique challenges facing LGBTQ+ youth (eg, concerns about experiencing stigma or discrimination as a minority^28^).

At present, the field concerning digital interventions among LGBTQ+ youth is small, yet those available are perceived as feasible, acceptable and relatively effective.^29^ However, most focus on physical health such as risk reduction or management of sexually transmitted illnesses (STIs^29^), with few concerning mental well-being.^30–33^ These mental health interventions are typically perceived positively by LGBTQ+ youth,^30 32–34^ with mixed findings reported by the three studies which considered the impact of the intervention on participants; (1) Rainbow SPARX^32^; (2) an online writing intervention^31^; and (3) QueerViBE.^30^ In their pilot trial, Rainbow SPARX (a didactic PC game using cognitive behaviour therapy principles) was associated with large reduction for depressive (d=1.01) and anxious (d=0.95) symptoms.^32^ QueerViBE (a series of brief, interactive videos designed for transgender and gender diverse youth) found a moderate decrease in psychological distress (d=0.63) when compared with the control group.^30^ However, the expressive writing intervention demonstrated no difference in depressive symptoms in their randomised controlled trial.^31^ Therefore, while limited, digital interventions are feasible, acceptable, and potentially effective for improving mental health among LGBTQ+ youth. However, there are currently no evidence-based digital interventions targeting LGBTQ+ youth who struggle with self-harm.

While self-harm among LGBTQ+ youth can be associated with multiple risks, complex experiences and unique stressors,^35–37^ a common issue is often emotional dysregulation.^38–41^ Experiencing difficulties with emotion regulation (ER) is a well-known transdiagnostic risk factor,^42–44^ which can be associated with higher risk of self-harm across ages, settings and genders.^45 46^ Typically, LGBTQ+ populations report greater difficulties with ER,^40 41^ which explains in part the association between LGBTQ+ identity and self-harm.^40 41^ Examining how ER can be better supported in young LGBTQ+ people who self-harm through digital intervention may be a helpful preventative strategy to aid LGBTQ+ youth broadly.

To address this, a pilot study was conducted with LGBTQ+ youth who had recent experiences of self-harmful thoughts and/or behaviours using an in situ, ER intervention device, Purrble,^47^ designed to provide in-the-moment support, see Intervention section for further details. Purrble was originally developed for children in moments of situated distress, but it has since been well-accepted across child and student populations delivering notable benefits for ER.^47–50^ Among a small sample of 21 LGBTQ+ young people, Purrble was found to be a feasible and acceptable intervention with continued device engagement across a 2-week deployment.^47^ Notably, access to Purrble was also associated with a reduction in anxiety symptoms and self-harmful thoughts. Qualitative data indicated that this was linked to Purrble supporting ER practices (eg, grounding, soothing) to prevent young people acting on their self-harmful urges and, in some cases, preventing them from considering self-harm at all.^47^ This is the only study to date which has explored the impact of a socially assistive robot (SAR) among LGBTQ+ youth, who are at risk of self-harm.^47^ Based on these findings and Purrble’s original design to support in situ, bottom-up ER,^48 49^ it appears that mental health outcomes such as anxiety and self-harm^47 50^ are guided by the proximal change in ER.

SARs have previously been used to support children in education,^51^ family^49^ or health settings,^52 53^ as well as adults with health conditions such as dementia or physical illnesses.^54 55^ These studies have shown promising results in the context of motivation, skill development and enhancement, as well as supporting mental health outcomes, for example, reducing loneliness and stress.^49–55^ Similarly, students and at-risk young people have described Purrble robots as a mechanism for comfort and distress relief.^47 50^ However, an ethical challenge raised in SARs literature is the use of these device as a replacement for humans, which could incur negative impacts considering social isolation.^56^ Therefore, research using SARs should be mindful of this, considering this influence in process analysis, and have additional procedures to prevent overreliance on these devices.

Although, early data relating to Purrble robots is promising,^47^ there is a lack of robust quantitative data on the impact of the Purrble robot in a wider sample of LGBTQ+ young people who have self-harmed. Evidence is therefore urgently needed to evaluate the efficacy of Purrble in (a) delivering measurable changes in ER when compared with a control group and (b) the extent to which this impacts the frequency of self-harmful thoughts and/or anxiety symptoms.

## Study objectives

### Primary objective

The primary objective of this study is to evaluate the impact of having access to the Purrble robot, compared with a waitlist control, on ER difficulties (Difficulties with Emotion Regulation Scale-8 (DERS8)) among LGBTQ+ young people with self-harmful thoughts.

### Secondary objectives

The secondary objectives are (1) to investigate the impact of having access to Purrble on changes to LGBTQ+ young people’s self-harmful thoughts over the trial period, in comparison to a waitlist control group and (2) to investigate the impact of Purrble on changes in symptoms of anxiety (Generalised Anxiety Disorder Questionnaire-7 (GAD-7)) and symptoms of depression (Patient Health Questionnaire (PHQ-9)) over the trial period, in comparison to waitlist controls. Finally, this will be the first opportunity to assess whether Purrble remains appealing and helpful to LGBTQ+ youth over an extended period.

## Methods

### Trial design

The study is a two-arm randomised controlled trial comparing an intervention group (Purrble robot) with a waitlist control group. The trial period is across 13 weeks, built of 3 pre-deployment assessments and 10 deployment assessments, using weekly, self-reported, validated surveys hosted by Qualtrics (see table 1). The intervention period will commence once Purrble has been deployed to the intervention group, week 4 (T1).

**Table 1 T1:** Overview of assessment design for both participant groups

Surveys	Pre deployment (weeks 1–3)			Deployment (weeks 4–13)				Follow-up (week 13+)
	T(−2)	T(−1)	T(0)	T1–T4	T5	T6–T9	T10	
Register interest+screening	X							
Consent	X							
Main assessment	X	X		X		X		
Extended assessment			X		X		X	
Qualitative interviews								X

Analyses will be conducted and reported in accordance with the Consolidated Standards of Reporting Trials (57 58), with consideration given to the recommendation of psychological interventions.^52^ Outcomes will be assessed 13 times across a 13-week period, including 3 baseline assessments and 10 weeks of deployment, with Purrble being delivered in time for week 4 (T1).

### Intervention

The intervention takes the form of an interactive plush toy-robot (figure 1), which was codesigned with children to support in-the-moment soothing.^48 49^ Purrble is framed as an anxious creature, in need of care and attention when it feels distressed. Embedded electronics are used to produce vibration patterns simulating heartbeats such as 1) frantic and anxious, and (2) slow, steady and relaxed. When held, the device emits a frantic heartbeat which can be slowed by stroking movements registered by embedded sensors. Once the device has been ‘soothed’ for long enough, the heartbeat transitions into a purring vibration, indicating a relaxed state. This transition can be achieved in less than 60 s but is dependent on the device–human interaction. Further details on the logic model underlying Purrble can be found in online supplemental material 1 or see previous research.^49^

10.1136/bmjopen-2023-079801.supp1Supplementary data

**Figure 1 F1:**
[figure not shown]
Purrble—socially assistive robot.

### Waitlist—control

The participants in the control group will be on a waitlist throughout the 13-week trial period. Once data have been collected at the final timepoint (week 13, T10), waitlist participants will receive a Purrble to keep. Waitlist control group was selected following discussions with Sprouting Minds members (see Patient and public involvement section).

### Participants

#### Eligibility criteria

When potential participants register their interest for the study, they will be asked demographic questions relating to the eligibility criteria, providing our information for our inclusion criteria. These are: (1) being between the ages of 16–25 years (inclusive); (2) identifying as any part of the LGBTQ+ umbrella; (3) having current experiences of self-harmful thoughts (eg, in the last month); (4) being able to read, write and speak English; and (5) living in the UK for the duration of the study. Exclusion criteria are being outside of the age range, identifying as heterosexual cisgender, not experiencing current self-harmful thoughts, being unable to understand English and living outside the UK.

#### Recruitment, randomisation and blinding

LGBTQ+ youth will be recruited to the trial by several strategies. These include: (1) approaching secondary schools and colleges, (2) social media adverts, (3) advertising through stakeholder charities and organisations (eg, Bounce Black, Harmless, King’s College London newsletter) and (4) online platforms (eg, MQ Participate). Those organisations which involve gatekeepers (eg, schools, colleges, charities, organisations) will be emailed by one of the leading researchers offering an introductory meeting to discuss the outline of study, explaining safeguarding protocols and how to share this information with young people. Young LGBTQ+ people will then be able to register their interest in the study, anonymously from gatekeepers. At recruitment, participants will not be blinded to the fact that Purrble was designed to support ER. The information sheet specifies that participants will be asked about mood, self-harm and ER over the course of the study.

Once eligibility is confirmed and young LGBTQ+ people have provided written informed consent (online supplemental material 2), they will be 1:1 randomly assigned to either intervention or waitlist control group, using a computerised algorithm. A stratification procedure will be applied to balance gender identity (transgender and gender diverse youth vs cisgender) across the two arms. The researcher conducting randomisation will be blind to treatment group allocation. However, the leading researcher and other team members who will be conducting safeguarding will be aware of group allocation. Researchers collecting outcome measures will be blinded to group allocation. Participants will be informed about their assigned condition. The intervention group will receive the Purrble before T1 data are collected, with waitlist participants receiving their Purrble devices after the 3-month follow-up data collection. Participants may withdraw at any time, once they have received their Purrble device it is theirs to keep.

In the event of change of circumstance, such as a serious adverse event (eg, they are hospitalised), participants are asked to inform the research team. During the follow-up surveys, a standard operation protocol will be used where the young person will be asked “Has your situation changed at all which might impact how you’d like to engage with the study?” via email, with the understanding that the research team will have time to arrange reasonable adjustments (eg, if a young person still wants to take part but is within an inpatient service).

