### Power analysis

Sample size was determined based on an a priori power analysis to detect a difference between the two arms when considering the primary outcome measure, DERS8. On the basis of a pilot with LGBTQ+ youth^47^ and other Purrble studies,^50 59^ we expect to see a medium effect size for this measure (d=0.4). This would indicate fewer difficulties with ER among young people who had access to Purrble.

With the anticipated medium effect size, simulations were performed involving a range of fixed and random effects. Simulations involved linearly increasing effect over the study period, and sensitivity analysis was performed over a range of scenarios considering the slope of effect change over time was either fixed or random. The simulation used a one sided t-test (=0.05) and targeted a sample size giving at least 80% power. The statistic to be compared between groups is the change in mean DERS8 Score in the 2 weeks preceding intervention (three assessments in total), to the mean DERS8 assessed at weeks 8, 9 and 10. The averaging over three assessments is intended to reduce the known variance in DERS8 when repeatedly assessed.^60^ Other simulations considered only comparing the change in DERS8 from baseline (week 0) to week 10, comparing the slope of the effect, assessed using simple linear regression. All simulations suggested better than 60% power with 70 participants per arm, with the mean change in DERS8 averaged over three assessments and the comparison of slopes, suggesting >80% power. The sample size of 140 is inflated by 20% to account for dropout rate,^61^ rounding up the total sample to 168.

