### Hypotheses

#### Primary hypothesis

Across the trial, we hypothesise that access to the Purrble intervention (compared with the waitlist control) will lead to a direct decrease in self-reported difficulties with ER as measured by the primary outcome (DERS8), averaged between three pre-deployment (weeks 1–3) and our final three deployment assessments (weeks 11–13).

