#### Statistical analyses

Testing the hypothesis that access to the Purrble intervention will lead to a reduction in emotion dysregulation, as measured by the composite primary outcome, will be done using a one-sided t-test.

As exploratory analyses, linear mixed models will be fitted to gain insight into how emotion dysregulation is altered with access to the intervention. In particular, we will regress the weekly outcome score on an indicator for the Purrble condition, a linear time trend and an interaction between the treatment indicator and time to examine differential trends in the two groups. We will adjust for baseline covariates and include participant-level random intercepts and slopes to account for persistent baseline differences between young people as well as person-specific time trends in the outcome. While the outcome is limited to DERS8 scores ranging from 8 to 40, we will model it as continuous data.

For secondary aims, we will use analogous linear mixed models to assess the impact of Purrble on relevant outcomes (cf., hypotheses above), adding baseline DERS8 as another covariate. We will not adjust for multiple comparisons, as these are exploratory aims meant to be generate hypotheses. Similarly, we will also assess the impact of access to Purrble on changes in proximal outcomes, as well as explore whether these appear to moderate changes on primary and secondary outcomes.

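### Randomisation is tied to consent and neither it nor disclosure of the arm is placed after T(0), so the self-reported baseline of the primary change score may be collected with knowledge of allocation

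*Protocol article*

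**What the plan says.** Recruitment, randomisation and blinding gives the order of events: "Once eligibility is confirmed and young LGBTQ+ people have provided written informed consent (online supplemental material 2), they will be 1:1 randomly assigned". Completing any pre-deployment survey is not a condition. The same paragraph adds "Participants will be informed about their assigned condition", with no time attached. The only event timed against the surveys is device delivery: "The intervention group will receive the Purrble before T1 data are collected".

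Trial design describes the schedule as "built of 3 pre-deployment assessments and 10 deployment assessments". Table 1 puts screening, consent and the first main assessment together in the T(-2) column, with T(-1) and T(0) following. It has no row for randomisation or for telling participants their arm. The Waitlist—control section has controls waiting for the whole 13 weeks, which include the three pre-deployment weeks.

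The primary endpoint uses those three weeks as its baseline. Power analysis defines the statistic as the "change in mean DERS8 Score in the 2 weeks preceding intervention (three assessments in total") to the mean at the last three assessments. The primary hypothesis gives the same windows: "averaged between three pre-deployment (weeks 1–3) and our final three deployment assessments (weeks 11–13"). Under Statistical analyses the hypothesis, "as measured by the composite primary outcome, will be done using a one-sided t-test".

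**The concern.** A baseline is protected from the effects of allocation if it is measured before allocation, or at least before the participant knows the result. Neither safeguard is written here. DERS8 is a self-report scale, participants are not blinded, and the protocol says they know at recruitment that Purrble was designed to support emotion regulation. A person told in week 1 that a device is coming, or that they must wait about three months, may answer differently in weeks 1–3. The primary statistic subtracts exactly those answers. Keeping the researchers who collect outcomes blind does not help, because the participant is the rater.

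There is a second, smaller consequence. Anyone who leaves during weeks 1–3 would already be a randomised participant, lost before any device could have been used.

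**Working it through.** **Sequence.**

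1. Trigger for randomisation: eligibility and consent (randomisation paragraph).
2. Time of consent: T(-2), week 1 (Table 1).
3. Control status: present through all 13 weeks (Waitlist—control).
4. Disclosure: yes, time not stated.
5. Device: before T1, week 4.

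Items 1 to 3 put allocation before T(-1) and T(0) on the natural reading. Consent and the first assessment share a column, so T(-2) could fall on either side of allocation; after it is more likely. Item 4 leaves open whether participants know their arm in weeks 1–3.

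**The plan's own figures.** 140 × 1.2 = 168 reproduces the total. The stated power above 80% comes from simulations whose variance components are not given, and the SD behind d = 0.4 is not stated, so that figure cannot be reproduced. As a benchmark only, take d = 0.4 on the SD of the change score, 70 per arm, one-sided 0.05, normal approximation:

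power = Φ(0.4 × √(70/2) − 1.645) = Φ(2.366 − 1.645) = 76.5%.

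If d is instead on the SD of a single score, with an assumed within-person correlation of 0.5 to 0.8, the averaged change has 98% power or more. The point here is bias, not sample size, and does not depend on which is right.

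**How a baseline shift enters.** Write the benefit as baseline mean minus final mean. Let b be the between-arm difference (intervention minus control) that allocation causes in the baseline mean, and p the fraction of it still present at weeks 11–13. Then

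observed contrast = true effect + b × (1 − p).

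The bias is b if the reaction has gone by the end and zero if it persists fully.

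**Size, assumed.** No document gives b. With p = 0 and b on the same SD as d:

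- 0.05 / 0.4 = 12.5%; 0.10 / 0.4 = 25%; 0.20 / 0.4 = 50% of the design effect.
- If T(-2) precedes allocation, only two of the three averaged scores can move. The range becomes 12.5% × 2/3 ≈ 8% to 50% × 2/3 ≈ 33%.

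On the benchmark above, with b in change-score SDs:

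| Size of b | Power if intervention baseline is lower (true d = 0.4) | Type I error if intervention baseline is higher (true d = 0) |
|---|---|---|
| 0 | 76.5% | 5.0% |
| 0.05 | 66.5% | 8.9% |
| 0.10 | 55.2% | 14.6% |
| 0.20 | 32.2% | 32.2% |

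**Early loss, assumed.** If 5% to 10% stopped during weeks 1–3, that would be 168 × 0.05 = 8.4 to 168 × 0.10 = 16.8, about 8 to 17 randomised participants in total across both arms.

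**The case against.** The strongest reply is that the article does not say when participants learn their arm. The sentence on disclosure comes directly before the one on device delivery, which fits notification near dispatch, after T(0), as well as notification at consent. If that is the practice, participants cannot react to their arm at baseline and the main bias disappears. The supplements are not shown, and a condensed article may omit the day of notification. This stands as far as it goes: a reader might infer that participants certainly know their arm throughout weeks 1–3, or that all three baseline scores certainly follow allocation, and the text supports neither as fact. It does not remove the point, because the article does state a trigger for randomisation, and that trigger precedes most of the baseline.

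Four further replies also stand:

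- The shift of 0.05 to 0.20 SD has no source in the documents, and its direction is unknown. Early relief in the device arm would bias towards no effect; the opposite shift would produce a false benefit.
- A reader might infer that any baseline reaction passes in full into the result. It does so only if it has gone by weeks 11–13.
- A reader might infer that early losses undermine the randomised comparison. The documents do not show that they would differ by arm, and the 20% inflation is there to cover loss of numbers.
- A reader might object to adjusting for a baseline measured after randomisation. The primary t-test has no stated covariates; adjustment appears only in the mixed models, for the exploratory DERS8 analysis and the secondary aims.

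The article already lists the lack of participant blinding as a limitation, but that does not address its reach into the baseline.

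**Conclusion.** The point holds as a weakness in the stated sequence, with a cheap improvement available. As written, allocation probably precedes at least T(-1) and T(0), nothing holds back disclosure until T(0) is submitted, and the primary change score uses those self-reported assessments as its baseline. The documents do not establish that the baseline will be contaminated. That requires three things they do not settle: disclosure before T(0), a reaction that differs between arms, and a reaction that fades by weeks 11–13. If all three occur, the bias could go either way. Under the assumed shifts it would be 12.5% to 50% of d = 0.4, or about 8% to 33% if T(-2) precedes allocation, with both quantities on the same SD. These figures are illustrations, not estimates. Early loss of already-randomised participants is possible, but the documents do not support calling it differential.

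**What to change.** Preferred: randomise after T(0) has been submitted and before devices are dispatched for T1. If dispatch lead time prevents this, randomise as planned but withhold the allocation from participants until T(0) is submitted.

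In either case, amend the randomisation paragraph to state both times and add rows for randomisation and disclosure to Table 1. If disclosure already follows T(0) in practice, one sentence saying so settles the question of knowledge at baseline.

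The cost of the preferred option is a tighter dispatch window between T(0) and T1, about one week on a weekly schedule. Delaying disclosure alone costs almost nothing, but leaves participants who drop out in weeks 1–3 as already randomised. The total of 168 and the nominal power are unchanged under both.
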